#### Interim analysis

For the interim analysis, the sample size was recalculated with doubling of the delta from 5 to 10 % to reduce the risk that the study is incorrectly aborted prematurely. Together with a lost to follow-up rate of 10 %, the total number of patients included for this analysis amounts 125.

An independent statistician will perform the interim analysis after a two-year follow-up of the first 125 included patients, because the total accrual is expected to complete within 3 years and because most regional recurrences occur within two years after initial treatment. According to the Haybittle-Peto boundary, a *P* value of 0.001 or less is considered statistically significant for this analysis [34]. Results of the interim analysis are reported to the DSMB.

#### Data safety monitoring board

The independent DSMB comprises a surgeon, medical oncologist, radiation oncologist and a statistician. The DSMB will meet annually to discuss the occurrence and nature of adverse events occurring during the study, initially at a 1-year interval. During the study, the DSMB may decide to change the frequency of discussion. All cases with a lesion that is highly suspicious for tumour recurrence on imaging, but not accessible for histology or cytology are presented to the DSMB for an independent review. Further, the DSMB is informed about the results of the interim analysis for further interpretation. DSMB recommendations are sent to the principal investigators. Should the principle investigators decide not to fully implement the DSMB recommendations, the principle investigators will send the recommendation to the accredited medical ethics committee, including a note to substantiate why (part of) this recommendation will not be followed.

#### Stopping rule

The right to discontinue the study prior to inclusion of the intended number of subjects is reserved to the principle investigators, but intends only to exercise this right for valid scientific or administrative reasons such as a negative advice for continuing the study by the DSMB, or disappointing accrual so that the total enrolment of 878 patients seems not feasible within the planned study period.

#### Final analysis

Primary and secondary endpoints will be analysed per protocol and in the intention to treat population after 5 and 10 years of follow-up. Primarily, uncorrected chi-squared statistics will be used to evaluate the null hypothesis. The chi-square test will be based on the Kaplan-Meier estimator, in case of censored data. Additionally, cox proportional hazards models and Kaplan Meier estimates will be used to analyse the outcome of both groups and to assess the univariable and multivariable association between prognostic variables, treatment and events, using the stratification factors. All statistical tests are 1-sided and a *P* value of 0.05 or less is considered statistically significant.

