## Methods

### Study design

The BOOG 2013–07 is a Dutch non-inferiority randomized controlled multicentre trial. Patients with clinically T1-2 invasive breast cancer, negative axillary ultrasound and limited SLN metastases, who are treated with mastectomy, are randomized to completion axillary treatment or no completion axillary treatment. Outcome will be evaluated after 5 and 10 years of follow-up. This study will be performed in 43 centres in the Netherlands. The study was conducted in accordance to the standards of Good Clinical Practice, in agreement with the Declaration of Helsinki and with Dutch law in general and with the Medical Research Involving Human Subjects Act (in Dutch: Wet Medisch-wetenschappelijk Onderzoek met mensen) in particular. This study was approved by the medical ethics committee of the Netherlands Cancer Institute - Antoni van Leeuwenhoek Hospital (PTC14.0032/M14CAT). The Board of Directors approved initiation of the study in current participating centres that are open for accrual (Additional file 1). The BOOG 2013–07 trial is registered at ClinicalTrials.gov (NCT02112682).

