### Consent and randomization

Eligible patients will be informed about the study aims, study procedures, possible adverse events, mechanism of treatment allocation, and their rights and responsibilities. After written informed consent is obtained, patients will be randomized between completion axillary treatment (control arm) and no completion axillary treatment (study arm).

Stratification factors for randomization include the following: age (≤50, 50 ≤ 75, >75), oestrogen receptor status (positive vs. negative), HER2neu status (amplified vs. not-amplified), lymph node metastasis (micro- vs. macrometastasis), clinical tumour size prior to any treatment (<3 cm vs. ≥3 cm), grading (grade I-II vs. III - according to modified Bloom-Richardson grading system), primary systemic therapy and participating centre.

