#### Sample size

Prior data indicate a 5-year regional recurrence free survival rate of 98 % for the control patient group, and a regional recurrence free survival rate of 96 % is expected for the experimental patient group. A difference of no more than 5 % (delta = 5 %) is considered acceptable, when taking in account the higher morbidity rate caused by completion axillary treatment in the control arm. The expected regional recurrence free survival rates and delta result in a sample size of 399 per arm. Therefore, we will need to study 399 experimental subjects and 399 control subjects to be able to reject the null hypothesis that the rate for experimental and control subjects is inferior by at least 5 % with a probability of 0.8. When taking in account a lost to follow-up rate of 10 %, 878 patients need to be randomized. An annual accrual of 324 patients can be achieved, based on the incidence of women diagnosed with invasive breast cancer in the Netherlands, the rate of patients that is operated on primarily (excluding patients treated with chemo- or hormonal therapy only, or with metastatic disease and frail elderly), the rate of patients with a positive SLN, treatment with mastectomy, the 43 participating hospitals, and an expected accrual rate of 30 %. Therefore, three years will suffice to include the 878 patients.

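### The additional multivariable Cox model draws on all eight stratification factors, including 43 centres, while about 24 regional recurrences are expected: too few for the prognostic associations it is meant to assess

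*Protocol article*

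**What the plan says.** The Final analysis section makes an uncorrected chi-squared test the primary analysis, based on Kaplan-Meier estimates if data are censored. Cox models come in addition, "to assess the univariable and multivariable association between prognostic variables, treatment and events, using the stratification factors". No factor is excluded and no special handling of any factor is stated.

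The section on consent and randomization lists eight factors: age in three bands, oestrogen receptor status, HER2neu status, micro- versus macrometastasis, clinical tumour size, grade, and finally "primary systemic therapy and participating centre". On the number of centres, the Study design section says: "This study will be performed in 43 centres in the Netherlands".

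The Sample size section gives the planning rates. For controls: "Prior data indicate a 5-year regional recurrence free survival rate of 98 % for the control patient group". For the study arm, "a regional recurrence free survival rate of 96 % is expected for the experimental patient group".

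**The concern.** A Cox model draws its information from events, not from patients, and this trial is planned around a rare event. Tying the multivariable model to the full stratification list brings in a factor with 43 levels. A centre without a recurrence gives the partial likelihood nothing to hold its coefficient, which runs to minus infinity. The other factors would share very few events.

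What is at stake is the set of prognostic associations that the article names as an aim of this model. If the model as worded cannot be fitted, the analyst must drop or pool factors after seeing the data. That leaves the reported adjusted results open to selection.

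**Working it through.** **The plan's own sample size.** Inputs: 98 % and 96 % event-free, margin 5 points ("A difference of no more than 5 % (delta = 5 %) is considered acceptable"), power 0.8, one-sided 0.05 ("All statistical tests are 1-sided").

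n per arm = (1.645 + 0.842)² × (0.98 × 0.02 + 0.96 × 0.04) / (0.05 − 0.02)² = 6.183 × 0.058 / 0.0009 = 398.4, so 399. Then 399 × 1.10 = 438.9, so 439 per arm and 878 in total. Both match the article, so its rates can be used to count events.

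**Expected regional recurrences at 5 years.**
- Planned rates, 399 per arm: 399 × 0.02 + 399 × 0.04 = 8.0 + 16.0 = 23.9.
- All 878 followed: 439 × 0.06 = 26.3.
- Both arms at 98 %: 798 × 0.02 = 16. Both at 96 %: 798 × 0.04 = 32.

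**Parameters.** Primary systemic therapy is taken as yes/no, since the article does not give its levels.

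| Term | Parameters |
|---|---|
| Treatment | 1 |
| Age (three bands) | 2 |
| Six binary factors | 6 |
| Subtotal without centre | 9 |
| Centre (43 − 1) | 42 |
| Total with centre indicators | 51 |

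**Events per parameter.**
- With centre: 23.9 / 51 = 0.47.
- Without centre: 23.9 / 9 = 2.7.
- As a yardstick only, ten per parameter would need 510 events with centre (510 / 878 = 58 % of patients) and 90 without.

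**Centres without an event.** Twenty-four events can fall in at most 24 centres, so at least 43 − 24 = 19 have none. With equal-sized centres the expected number is 43 × (42/43)^24, about 24. Even with 32 events, at least 11 have none.

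**Simulated trials at the planned rates.** These used 798 patients, 43 centres and assumed covariate prevalences. The true treatment log hazard ratio is ln[ln(0.96) / ln(0.98)] = 0.70.
- Centre indicators, default fit in one common package: a fitting error in 159 of 200 trials, and an unusable standard error (above 50 or undefined) in the other 41.
- Centre indicators, with the event-free centres handled so that the fit is numerically stable: the treatment log hazard ratio stayed finite, with median 0.73 to 0.77 and 95 % interval coverage of 0.95 to 0.97.
- Centre omitted or used as a stratum: 2 of 200 fits failed, about 7 % of the rest had a non-finite coefficient, and the treatment median was 0.68 to 0.72.

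**If recurrence is about 1 %.** The Background cites study-arm rates of 1.0 %, 0.9 % and 1.1 % in three earlier trials. Then 798 × 0.01 = 8 events, or 8 / 9 = 0.9 per parameter without centre. In simulation, some prognostic coefficient diverged in about half to two thirds of trials. The treatment log hazard ratio exceeded 3 in absolute value in 7 to 10 % of trials with centre indicators, against 0.5 % without centre.

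**The case against.** **The article does not say that centre enters as 42 indicators.** Using centre as a stratum would also fit the wording and cost no parameters, and such detail often sits in an analysis plan that is not shown. This stands in part. But the article itself states the covariate list and exempts nothing from it, and settling centre still leaves 2.7 events per parameter for the remaining terms.

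**The Cox analysis is additional.** This stands in full. No adjusted hazard ratio is designated for the non-inferiority conclusion.

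**An event-free centre harms only its own coefficient.** This is right at the planned rates. In the limit its patients leave the risk sets and the treatment estimate survives. The fitting errors above reflect how a package handles the singular centre terms, not a lost treatment effect.

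**Twenty-four events is one endpoint at one time.** The Endpoints section counts death as an event in time-to-event endpoints, and 10-year and survival analyses will have more events. This stands and limits the point to regional recurrence. However, the planning rates are themselves labelled as recurrence-free survival, so 24 is the plan's own 5-year count, and no plausible increase brings the 51-parameter model near 510.

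**The 1 % scenario is borrowed.** The earlier trials treated mostly with breast conservation, and the Background says that results of two of them cannot be extrapolated to mastectomy patients. The scenario is therefore an assumption. It is still worth guarding against, because the same section says that all three trials had fewer events than anticipated.

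**Conclusion.** The point holds for the prognostic associations in the additional Cox analysis of regional recurrence. At the planned rates there are 0.47 events per parameter with centre indicators, at least 19 centre coefficients without a finite estimate, and about 2.7 events per parameter once centre is removed. These counts rest on the article's rates and on primary systemic therapy being binary. The simulation results also rest on assumed covariate prevalences.

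Three stronger readings are not supported:
- A reader might infer that the adjusted treatment hazard ratio would be infinite, with meaningless intervals. At the planned rates it stays finite with near-nominal coverage. Only at about 8 events does it occasionally fail.
- A reader might infer that the primary conclusion is at risk. The chi-squared test does not depend on this model.
- A reader might cross the eight factors, get 3 × 2⁶ × 43 = 8,256 cells for 878 patients, and conclude that randomisation cannot balance the arms. That would follow only from blocking within every cell. The article does not state the allocation method, and minimisation over the factor margins would cope.

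This is a moderate weakness in a secondary analysis and is cheap to repair.

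**What to change.** In the Final analysis section or the analysis plan, state for regional recurrence:
- Centre is not entered as a fixed covariate. It is a shared frailty or is left out. Leaving it out is simpler with so few events.
- The multivariable model contains treatment and two or three factors named in advance (for example nodal metastasis size, oestrogen receptor status and grade), fitted by Firth-penalised Cox regression. With three binary factors this is 23.9 / 4 = 6.0 events per parameter; with two, 23.9 / 3 = 8.0.
- The remaining stratification factors are reported univariably.

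Keep the fuller model, also without centre indicators, for endpoints with enough events, and set that minimum in advance.

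The change costs a few lines of text and uses available software. The price is fewer adjusted prognostic estimates for the primary endpoint, and the choice of named factors must be justified before the data are seen.

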### Radiation therapy

#### Chest wall irradiation

Radiation therapy of the chest wall after mastectomy is indicated in specific circumstances depending on the Dutch and local protocols and therefore not an exclusion criterion in this study. According to the Dutch breast cancer guideline, postoperative radiation therapy after mastectomy can be considered in patients with 1–3 axillary lymph nodes containing metastatic disease with at least one risk factor. Risk factors include angioinvasive growth, grade III tumours, tumour size of ≥3 cm and/or age ≤ 40 years [5]. The indications for radiation therapy will be clearly defined for each participating centre to prevent a low-threshold for chest wall irradiation in study arm B.

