### Statistics

#### Endpoints

Regional recurrence rate is the primary endpoint in this study. Secondary endpoints include number of delayed axillary treatment, distant-disease free survival, overall survival, local recurrence rate, other-regional recurrence rate, contralateral breast cancer rate, percentage difference in the administration of postoperative radiation therapy, axillary morbidity rate and quality of life. The events included in the definitions of the different recurrences are provided in Table 1, and are based on the Maastricht Delphi Consensus on Event Definition by Moossdorff et al. [32, 33]. Pathological confirmation of a regional recurrence is mandatory, and recommended in case of other suspicious lesions. All cases with a lesion that is highly suspicious for tumour recurrence on imaging, but not accessible for tissue sampling are presented to the Data Safety Monitoring Board (DSMB) for an independent review.

**Table 1 Tab1:** Definition of a regional, other-regional, local and distant recurrence

Classification	Events included
Regional recurrence	Recurrence in an ipsilateral axillary-, infraclavicular-, or supraclavicular lymph node
Other-regional recurrence	Recurrence in an ipsilateral internal mammary lymph node
Local recurrence	Recurrence in skin or subcutaneous tissue on the ipsilateral chest wall
Distant recurrence	Recurrence in any other location, including recurrence involving the
	sternal bone, or contralateral lymph nodes

Time to event endpoints are defined as the time interval between the date of randomization and the date of first suspicion of the predefined recurrence, or the date of death, whichever comes first, measured in days. Patients in whom recurrence is not observed and are still alive are censored at the date of last follow-up. Death from breast cancer and its treatment, death from a second primary invasive non-breast cancer, and death from other- or an unknown cause are recorded.

Administration of postoperative radiation therapy is registered and the percentage difference between both study arms is recorded. Axillary morbidity rate will be assessed using a validated questionnaire and by predefined adverse events that are recorded by the treating physician. Quality of life will be assessed using validated questionnaires.

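### The one-sided 0.05 rule suits the primary non-inferiority test but is applied to every test, with no direction fixed for secondary endpoints or prognostic factors (minor)

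*Protocol article*

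**What the plan says.** The Final analysis section sets the scope first: "Primary and secondary endpoints will be analysed per protocol and in the intention to treat population after 5 and 10 years of follow-up". It adds Cox models and Kaplan-Meier estimates to "assess the univariable and multivariable association between prognostic variables, treatment and events, using the stratification factors". It then ends with the rule: "All statistical tests are 1-sided", and a P "value of 0.05 or less is considered statistically significant".

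The Endpoints section shows how much falls under that rule: "Secondary endpoints include number of delayed axillary treatment, distant-disease free survival, overall survival, local recurrence rate, other-regional recurrence rate", then contralateral breast cancer, then "percentage difference in the administration of postoperative radiation therapy, axillary morbidity rate and quality of life".

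Nothing in the article limits the one-sided rule to the primary test. No section names a test direction for a secondary endpoint or a prognostic variable. The only other significance level is 0.001 in the Interim analysis section, so 0.05 governs the final analyses.

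**The concern.** A non-inferiority test is one-sided by construction: it has a margin and a single direction of concern. The secondary and prognostic analyses do not share that structure. For survival the question is whether the study arm does worse. For morbidity and quality of life the hope is that it does better. For a prognostic variable the document states no expectation at all. One sentence that names no direction cannot serve all of these.

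What is at stake is how the secondary results may be read. As written, a reader of the final report cannot tell whether a one-sided P value below 0.05 came from a direction chosen in advance or from the direction that the data happened to show. These two cases have different error rates. For some of the stratification factors the rule cannot be carried out at all.

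**Working it through.** **1. Is one-sided 0.05 the design level of the primary test?**

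Inputs from the Sample size section: a "5-year regional recurrence free survival rate of 98 % for the control patient group", 96% for the experimental group, a margin of 5 percentage points, power 0.8 and equal arms. That section gives no alpha, so the level comes from Final analysis.

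Formula (unpooled variance): n per arm = (z_alpha + z_power)² × [p1(1 − p1) + p2(1 − p2)] / (margin − (p1 − p2))².

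- Variance term: 0.98 × 0.02 + 0.96 × 0.04 = 0.0196 + 0.0384 = 0.0580.
- Distance to the margin: 0.05 − 0.02 = 0.03, squared 0.0009.
- One-sided 0.05: (1.645 + 0.842)² × 0.0580 / 0.0009 gives 399 per arm after rounding up. This matches the protocol.
- One-sided 0.025: (1.960 + 0.842)² × 0.0580 / 0.0009 gives 506 per arm. This does not match, and 399 per arm would then have 70.1% power.

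One-sided 0.05 is therefore the level on which the primary comparison was sized.

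**2. What does the rule do to a single-degree-of-freedom secondary or prognostic test?**

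The one-sided 0.05 critical value is 1.645, the same as for a two-sided 0.10 test. The two-sided 0.05 critical value is 1.960. The consequences below are alternatives; no single test can suffer both.

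- *Direction fixed in advance.* The false-positive rate stays at 5%, but an opposite effect cannot be declared. At z = −3 against the chosen direction, one-sided P = 1 − Φ(−3) = 0.9987, while two-sided P = 2 × Φ(−3) = 0.0027.
- *Direction read from the data.* The test rejects when |z| exceeds 1.645, so the false-positive rate is 2 × 0.05 = 0.10 instead of 0.05.

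The article does not say which applies.

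**3. What about factors with more than two levels?**

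The models use the stratification factors. Consent and randomization lists age in three groups and participating centre among them; Study design gives 43 centres. Entered as categories, an overall test has 3 − 1 = 2 degrees of freedom for age and 43 − 1 = 42 for centre. Such a statistic is a squared distance without a sign, so it has no one-sided version. Age entered as a single trend would fall under step 2.

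**The case against.** The strongest defence is that directions are partly implied. The Background and the abstract's Discussion expect less morbidity and better quality of life, without a cost in survival. Chest wall irradiation asks each centre to define its indications "to prevent a low-threshold for chest wall irradiation in study arm B". On that reading the natural one-sided tests for survival and radiotherapy use look for harm, or for excess use, in the study arm. They would do so at z = 1.645, and a two-sided test would be less sensitive. This stands as far as it goes. It does not reach the prognostic factors, and an implied hypothesis is not a direction fixed for a test.

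Three stronger readings are tempting, and the documents do not support them.

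- A reader might infer that the rule hides harm, because a test aimed at benefit cannot show worse survival or extra irradiation in the study arm. Nothing aims those tests at benefit; the text points the other way.
- A reader might compute a family-wise error over the nine secondary endpoints. That would need independence, yet overall and distant-disease-free survival overlap, and the time-to-event definitions share deaths. Nine is also not the number of tests, given two populations and two time points. Most of such a figure would be multiplicity, which two-sided testing does not remove.
- A reader might fault the lack of margins for secondary endpoints. A protocol article may leave those to a fuller document, so their absence is no error.

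It is also fair that the article describes the radiotherapy difference as recorded and names no specific test for quality of life. Both come under the rule only because they are listed as secondary endpoints to be analysed.

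**Conclusion.** The point holds as a minor one. The article states, without exception, a rule that fits one test and misfits the rest. For each single-degree-of-freedom secondary or prognostic test, the result is either an opposite effect that cannot be declared or a false-positive rate of 10% rather than 5%. For overall tests of multi-level factors the rule is undefined.

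The 10% figure assumes a normally distributed test statistic and a direction chosen after seeing the data. The article does not plan that choice, but it does not exclude it either. A separate analysis plan, not shown, might set other levels; the present wording leaves no room for them. The primary comparison, its one-sided 0.05 level and the 399 per arm are unaffected.

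**What to change.** Replace the closing rule of Final analysis with wording such as:

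*The primary non-inferiority test is one-sided at 0.05. Secondary endpoints and prognostic factors are reported as supportive results with two-sided 95% confidence intervals and two-sided P values.*

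This changes one sentence and adds no patients. The downside is that the critical z for these results rises from 1.645 to 1.96. A harm signal with z between those values would be significant in a one-sided test directed at harm in advance, but not in the two-sided test. The confidence intervals would still show effects in both directions.
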